### Outcome Measures

Each participant will attend six assessment days in total as follows: baseline (week 0) and week 3, week 5, week 8, week 16, and week 24 posttreatment sessions. At each assessment day, three assessments will be given to the participant in the following fixed sequence: ADAS-Cog, verbal fluency test, and Stroop test. Only the patient and the research personnel designated to administer assessments will be in the room during assessments. At the baseline and week 5 and week 16 posttreatment assessments, additional caregiver assessments will be performed. Alzheimer Disease Co-operative Study-Activities of Daily Living Inventory (ADCS-ADL) and Neuropsychiatric Inventory Questionnaire (NPI-Q) assessments will be performed at each of these visits (in that order), while the Treatment Satisfaction Questionnaire for Medication (TSQM) will only be used at the week 5 assessment. These outcome measures must be administered to the same caregiver at each visit. If a participant is accompanied to an assessment visit by someone other than their usual caregiver, the assessor will contact the usual caregiver by phone to complete these assessments.

All assessments will be performed on a Monday or the first working day of the week. Note that the specific dates of the last three assessments (the follow-up assessments) will be adjusted based on whether the participant is in a 2-week or 4-week treatment group. An assessor will be assigned to each participant. That same assessor must perform all of the six assessments with the assigned participant. Deviations should be justified (changes in staff, assessor illness, etc), and an explanation will be documented in the assessment notes.

As participant schedules are often busy, we can adjust the specific dates of the assessments within ranges (Table 1). If no assessment is possible within these windows, the assessment will be skipped and the data point will be missing from the analysis (with the exception of the baseline assessment, which will require rescheduling the treatment).

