#### Analysis of the Results

Baseline characteristics will be assessed between the active and sham treatment groups by descriptive statistics, as well as formal statistical tests. Baseline differences between the two groups, if any, will be adjusted for in the final statistical analyses. All assessment scores will be checked for normality of distribution to determine the choice of either parametric or nonparametric methods. Bartlett statistic will be used to assess the homogeneity of variances, and Levene [56] or Brown-Forsythe [57] tests, which are less sensitive to departures from normality, may also be used. In all instances, a *P* value <.05 will be considered significant.

To test H1 and H2 (the efficacy of rTMS treatment), two-factor (active vs sham) repeated (pre-post treatment) analysis of variance (ANOVA) will be used to investigate the effect of treatment before and after the 4-week block of treatment. The dependent variable will be the change in the ADAS-Cog score (primary outcome measure). Testing H3 will be similar to the tests of H1 and H2, but the two factors will be the two durations of treatment.

For secondary outcome measures, a two-factor ANOVA will also be used in the same way as described above, but a Hochberg test [58] will be applied to correct for multiple comparisons.

The last-observation-carried-forward method will be used in the case of missing data or premature termination.

To test H4 (the durability of rTMS treatment), repeated measure ANOVA will be used among responders (those who show improvement in the ADAS-Cog score of ≥3 points over the course of treatment [3] in both groups) to investigate the duration over which the improvement may last. Post-hoc follow-up methods, such as Dunnett [59] and Tukey [60] tests, will be applied as needed. In addition, a mixed regression model will be developed to predict the response variable at each assessment visit of the active treatment group (both treatment arms separately). The independent variables will be patients’ current age and the severity of Alzheimer disease (as measured by the CDR).

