To test H5 (the correlation of treatment effect and severity), we will run regression and correlation analyses between the severity of Alzheimer disease (the MoCA and CDR scores) at baseline and the change in the ADAS-Cog score. The correlation coefficient (either the Pearson or Spearman correlation coefficient, whichever is more appropriate) and its statistical significance will be determined. Sensitivity of the regression and correlation analyses with respect to the data distribution will be assessed. Influential observations and outliers, if any, will be identified.

The above statistical analysis will also be repeated for secondary outcome measures after correcting for multiple comparisons. In addition, covariate analysis will be performed in an appropriate manner. Covariance balance (or imbalance) is checked with the ANOVA test when there are three or more groups or by the *t* (or the approximate Z) test when there are only two groups. For the ANOVA test, we will first check the satisfaction of ANOVA assumptions (such as normality of distribution and equality of variances). If any violation is found, transformations will be made before the ANOVA test. If covariance imbalance is statistically significant, the final data analysis will be adjusted for covariance imbalance (eg, by the use of regression analysis with these imbalanced covariates as explanatory variables).

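### Durability is tested by repeated-measures ANOVA over unevenly spaced visits with no check of sphericity; if correlation falls with time, a pooled error term mis-sizes the visit-specific standard errors

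*Protocol article*

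**What the plan says.** The durability hypothesis is H3 under Study Goal, Objectives, and Hypotheses and is labelled H4 under Analysis of the Results. It is specific to visits: an effect is expected to remain at 8 weeks, but not necessarily at 16 and 24.

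Under Analysis of the Results, "repeated measure ANOVA will be used among responders". Responders are "those who show improvement in the ADAS-Cog score of ≥3 points over the course of treatment". Then "Post-hoc follow-up methods, such as Dunnett [59] and Tukey [60] tests, will be applied as needed". The general significance rule is that a P "value <.05 will be considered significant".

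Outcome Measures sets the visits: "baseline (week 0) and week 3, week 5, week 8, week 16, and week 24 posttreatment sessions". Counted from baseline, the gaps are 3, 2, 3, 8 and 8 weeks.

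Two kinds of assumption check are named: "All assessment scores will be checked for normality of distribution to determine the choice of either parametric or nonparametric methods", and "Bartlett statistic will be used to assess the homogeneity of variances", with Levene or Brown-Forsythe as options. A later list of ANOVA assumptions is open-ended, but it is written for covariate balance and does not name sphericity. A mixed regression model is added, but its purpose is to predict response in the active arms from age and CDR, not to test how long the effect lasts.

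**The concern.** Univariate repeated-measures ANOVA uses one pooled within-patient error term. Follow-up comparisons based on that term give every between-visit difference the same standard error. This is right only if all those differences have the same variance. Here some visits are 2 weeks apart and others 24, in a progressive disease, so change over a long gap may well vary more than change over a short one. A test for equal variances cannot detect this: the visits can have identical variances while the differences between them do not.

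Because the hypothesis asks which visits still show an effect, the standard error at each visit decides the answer. One that is too small at week 24 makes statements about late persistence or loss look firmer than they are. One that is too large at week 8 makes the estimate there look less precise than it is.

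**Working it through.** The protocol states no error rate, correlation or responder count for this analysis, so there is no figure of its own to reproduce. The check works out how far a pooled standard error would be wrong.

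**Inputs**
- From Outcome Measures: visits t = 0, 3, 5, 8, 16, 24, counted in weeks from baseline.
- From Sample Size Estimation: SD 4.9 points. I assume it is the SD of change from baseline to week 5.
- Assumed: 50 responders in one group, complete data, no treatment effect, a pooled error term and baseline as reference.
- Assumed covariances: random slopes with SD 0.15 or 0.25 points per week; serial correlation of 0.95 per week; and compound symmetry as the control.

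**Step 1: formula.** Twice the expected pooled error equals the mean of Var(Yi − Yj) over the 15 visit pairs. If the true SD of change at a visit is s and the pooled SD is p, a nominal 95% interval misses with probability about 2Φ(−1.96·p/s).

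**Step 2: unselected patients.** With random slopes, Var(Yi − Yj) = b²(ti − tj)² + 2σ². The mean squared gap is (6 × 930 − 56²)/15 = 2444/15 = 162.9.
- b = 0.15: 2σ² = 24.01 − 0.0225 × 25 = 23.45. Pooled variance = 0.0225 × 162.9 + 23.45 = 27.11, so p = 5.21. Week 8: s = √(1.44 + 23.45) = 4.99, miss 4.1%. Week 24: s = √(12.96 + 23.45) = 6.03, miss 9.1%.
- b = 0.25: 2σ² = 24.01 − 0.0625 × 25 = 22.45. Pooled variance = 0.0625 × 162.9 + 22.45 = 32.63, so p = 5.71. Week 8: s = √(4 + 22.45) = 5.14, miss 2.9%. Week 24: s = √(36 + 22.45) = 7.65, miss 14.3%.
- Compound symmetry: p = s = 4.9 at every visit, miss 5.0%.

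**Step 3: responders, as planned.** I kept simulated patients who improved by at least 3 points from baseline to week 5 (27% of them), formed groups of 50, and counted how often the pooled 95% interval missed the responders' own true mean change (30,000 groups, or as many as the simulated pool allowed).

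| Covariance | Pooled SD | SD, week 8 | SD, week 24 | Miss, week 8 | Miss, week 16 | Miss, week 24 |
|---|---|---|---|---|---|---|
| Random slope 0.15 | 4.84 | 4.46 | 5.47 | 3.3% | 5.1% | 8.2% |
| Random slope 0.25 | 5.34 | 4.54 | 6.90 | 2.1% | 5.7% | 12.9% |
| Serial 0.95 per week | 6.08 | 4.50 | 8.17 | 0.9% | 8.9% | 14.6% |
| Compound symmetry | 4.52 | 4.41 | 4.42 | 4.8% | 4.4% | 4.6% |

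The formula agrees. For slope 0.25 at week 24, 1.96 × 5.34/6.90 = 1.517, which gives 12.9%. At weeks 3 and 5 the pooled interval is also too wide (misses of 0% to 3% under the three non-symmetric covariances). With visit-specific (paired) standard errors, the miss rate at weeks 8, 16 and 24 is 4.8% to 5.2% in all four cases.

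**Step 4: what selection does.** In the same data, with no treatment effect, the responders' mean change at week 5 is −6.0 points. With 50 responders, pooled tests against zero change reject in at least 98% of groups at every follow-up visit from week 5 on. Paired tests reject in at least 93%. This is a shift in the mean, not a fault in the standard error.

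**The case against.** The strongest reply is that this is detail an article leaves to the analysis plan. A sphericity correction, the error term, the reference visit and the covariance structure commonly belong there, and the follow-up tests are worded loosely. That stands as far as it goes: the lack of a stated correction would be a weak point by itself. But the article does fix the method, its follow-up tests and its checks. A Greenhouse-Geisser correction brings the overall F test back to 4.4% to 4.9% in simulation, yet it leaves a pooled standard error in the visit contrasts, and those are what the hypothesis needs.

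Second, the size depends on assumptions. This stands. Under compound symmetry there is almost nothing to see. With week 5 as reference the profile changes: in unselected patients (n = 40) with serial correlation of 0.5 to 0.9 per 8 weeks, the error at nominal 5% is 0.0% to 0.3% at week 8, about 6% at week 16 and 10.5% to 13.8% at week 24. The direction at week 24 holds. Last-observation-carried-forward and a group factor were not modelled.

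Third, a reader might infer more than the documents support:
- That false-positive rates are too low at weeks 5 to 8 and power is lost at week 8. This is not so for the planned analysis. Selection on the same score pushes rejections against baseline close to 100% with 50 responders (Step 4); only the standard error is too large there.
- That equality of variances is the only thing checked. Normality is checked too, with a possible switch to nonparametric methods.
- That a better model would make the durability result interpretable. It would not, because the selection effect remains.

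**Conclusion.** The concern holds as a point about standard errors. The named method is poorly matched to visits spaced 2 to 24 weeks apart, and the named checks cannot reveal the mismatch. If within-patient correlation falls with time, pooled 95% intervals for the responders' mean change miss about 1% to 3% of the time at week 8 and about 8% to 15% at week 24. If correlation is the same at all gaps, they miss about 5% at weeks 8 to 24. These figures assume 50 responders, a pooled error term, baseline as reference and SD 4.9 for change at week 5; the documents establish none of these for the durability analysis.

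The weight is minor to moderate. It bears on a stated study hypothesis, but not on the primary comparison of active with sham treatment.

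**What to change.** Replace the repeated-measures ANOVA and its pooled-error Dunnett or Tukey follow-ups with a mixed model for repeated measures: visit as a categorical factor, unstructured covariance and Kenward-Roger degrees of freedom. Take the week 8, 16 and 24 contrasts from it with visit-specific standard errors, adjusted for the three comparisons, and name the reference visit. Use the same hypothesis label in both sections.

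The cost is wording and standard software, with no new data. The small downside is more covariance parameters: 6 × 7/2 = 21 for six visits. If responders are few, a simpler covariance structure or paired visit-specific contrasts would serve. The text should also say that this change does not address selection of responders on the outcome being followed, which needs separate treatment.

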### Study Goal, Objectives, and Hypotheses

The overall goal of this study is to compare the efficacy of high-frequency active versus placebo rTMS for the treatment of cognitive impairment among people with mild to moderate Alzheimer dementia. The specific objectives and hypotheses of the study are as presented below.

First, estimate the difference in treatment effects among patients treated with active as compared with placebo high-frequency rTMS applied bilaterally to the DLPFC. Hypothesis 1 (H1) is as follows: better cognitive performance will be seen in patients randomly assigned to the active treatment group compared with those assigned to the placebo group.

Second, estimate the difference in treatment effects for patients receiving 4 weeks of rTMS versus 2 weeks of rTMS. Hypothesis 2 (H2) is as follows: four weeks of rTMS will be more effective than 2 weeks of rTMS in improving cognitive function.

Third, estimate the duration of treatment effects among responders to active rTMS, where response is defined as improvement in the ADAS-Cog of ≥3 points. Hypothesis 3 (H3) is as follows: treatment effects will still be detectable 8 weeks postintervention, although not necessarily at 16 and 24 weeks postintervention.

Fourth, estimate the effect of dementia severity on treatment outcomes among patients receiving active rTMS. Hypothesis 4 (H4) is as follows: the effect size will be greater in participants with a clinical dementia rating (CDR) of 1 than in those with a CDR of 2.

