### Randomization

Once enrolled in the study, each participant will be assigned to a treatment group (either sham or active, as well as either 2 or 4 weeks of treatment), using stratified block randomization (block size of 3). There will be four distinct stratification blocks using two levels for two factors (age and severity) as follows: age ≥70 years, CDR=1; age ≥70 years, CDR=2; age <70 years, CDR=1; age <70 years, CDR=2.

Group assignment will be determined using an automated algorithm. The only person who will know the group assignment for a given participant is the rTMS administrator at each site who provides the age and CDR data for the algorithm and informs the participant of the duration of treatment. Blinding of the site coordinator will be broken only when necessary to ensure patient safety, that is, in case of a serious adverse event where clinical follow-up is necessary.

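### The severity hypothesis is about the rTMS effect by CDR level, but the stated test relates severity to raw ADAS-Cog change without a sham contrast, so it cannot separate prognosis from effect modification.

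*Protocol article*

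**What the plan says.** Under Study Goal, Objectives, and Hypotheses, the fourth objective is to "estimate the effect of dementia severity on treatment outcomes among patients receiving active rTMS". The hypothesis attached to it (H4) is that "the effect size will be greater in participants with a clinical dementia rating (CDR) of 1 than in those with a CDR of 2".

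Under Analysis of the Results, the matching test is numbered H5 and introduced with the words "To test H5 (the correlation of treatment effect and severity". What follows is "regression and correlation analyses between the severity of Alzheimer disease (the MoCA and CDR scores) at baseline and the change in the ADAS-Cog score". The inferential step is this: "The correlation coefficient (either the Pearson or Spearman correlation coefficient, whichever is more appropriate) and its statistical significance will be determined". The same section sets significance at P below .05 and repeats the analyses for the secondary outcomes after a multiplicity correction.

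Severity enters one other stated model. In the durability analysis, "a mixed regression model will be developed to predict the response variable at each assessment visit of the active treatment group", with predictors "current age and the severity of Alzheimer disease (as measured by the CDR". That model is also confined to active patients.

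Under Randomization, severity is a stratification factor: "There will be four distinct stratification blocks using two levels for two factors (age and severity", where the severity levels are CDR 1 and CDR 2.

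**The concern.** In a sham-controlled trial a treatment effect is an active-minus-sham difference. A claim that the effect is larger at CDR 1 than at CDR 2 is therefore a difference between two such differences. Change from baseline in a treated patient is not a treatment effect. It also contains whatever that patient would have done without rTMS.

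If CDR 1 and CDR 2 patients would change by different amounts anyway, for instance through different rates of decline or different room to move on the scale, a severity-change correlation picks that up. It could appear to support H4 when the benefit is the same in both strata, or when there is none. If the natural difference runs the other way, it could hide a real modification. The plan as written cannot tell these cases apart. Because the analyses are repeated for the secondary outcomes, the problem carries over to them.

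**Working it through.** **What each analysis estimates.** Let g be the difference in mean ADAS-Cog change between CDR 2 and CDR 1 without rTMS, and e the difference in rTMS effect between the strata. H4 concerns e.

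- Severity contrast in active patients: estimates g + e.
- Severity contrast in sham patients: estimates g.
- Arm-by-CDR interaction (active contrast minus sham contrast): estimates (g + e) − g = e.

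**Inputs.**
- From Sample Size Estimation: SD 4.9; 63 per group, so 2 × 63 = 126 active and 63 sham; expected effect 3 points.
- From Analysis of the Results: significance at .05, taken here as two-sided.
- Assumed, because the documents do not give them: g from 0 to 3 points, and a CDR 2 share of 30% or 50%.

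The article states no power or sample size for the severity test, so there is no plan figure to reproduce for it. The 63 per group is used as given.

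**Active-only test, equal benefit in both strata (e = 0).**

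SE = 4.9 × √(1/n₁ + 1/n₂), where n₁ and n₂ are the active patients at CDR 1 and CDR 2; noncentrality = g / SE; 124 degrees of freedom.

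- 50% share: n₁ = n₂ = 63, SE = 4.9 × √(2/63) = 0.873. For g = 0.5, 1 and 2 the noncentrality is 0.57, 1.15 and 2.29.
- 30% share: n₁ = 88, n₂ = 38, SE = 4.9 × √(1/88 + 1/38) = 0.951. The noncentrality is 0.53, 1.05 and 2.10.

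Rejection rates, simulated with 20,000 trials per setting and a 3-point benefit in both strata:

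| g (points, assumed) | Active only | All arms pooled, no arm term | Arm-by-CDR interaction |
|---|---|---|---|
| 0 | about 5% | 4% | about 5% |
| 0.5 | 8-9% | 8-10% | about 5% |
| 1 | 18-21% | 22-27% | about 5% |
| 2 | 55-62% | 70-78% | about 5% |
| 3 | 88-93% | 97-99% | about 5% |

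Ranges span the two CDR shares. The noncentral t distribution gives the same active-only figures (for example 8.8%, 20.6% and 62.3% at the 50% share). The mean active-only contrast tracked g closely; the mean interaction stayed at about 0.

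**Power of the interaction (g = 0, e not zero).**

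SE = 4.9 × √(1/n₁ + 1/n₂ + 1/m₁ + 1/m₂), where m₁ and m₂ are the sham patients at each CDR level.

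- 50% share: sham 31 and 32, SE = 1.51.
- 30% share: sham 44 and 19, SE = 1.65.

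Simulated power is 44-50% for e = 3 points and 15-17% for e = 1.5 points.

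**Does another stated analysis supply the sham contrast?** The durability mixed model is active-only. The covariate adjustment enters imbalanced baseline covariates as explanatory variables, which adds main effects and no interaction. Neither does.

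**The case against.** **The test fits the objective.** The objective speaks of outcomes among patients on active rTMS, and relating severity to change in those patients answers that prognostic question. This stands as far as it goes, and the correlation is legitimate as a description. But H4 and the label on the test both speak of a treatment effect, and the correlation does not measure one.

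**The article is condensed and does not list every model term.** It does not say which arms enter the severity analysis, and it promises appropriate covariate analysis. A reader might infer that the sham data are deliberately set aside; the text supports only that no sham contrast is stated. For the Pearson or Spearman coefficient the lack of an arm term is plain. For the regression one can say only that none is named. The defect does not depend on which arms are used, since pooling all arms without an arm term shares it. Nor is this detail left to another document: the article names the test, its statistic and the significance level.

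**The natural difference is assumed.** This stands. A reader might infer that the plan will produce a false severity finding. The documents do not support that: at g = 0 the test keeps its 5%, and the 55-62% figure needs a natural difference two thirds the size of the planned 3-point effect. Regression to the mean is not established as a source either, because severity is graded on CDR and MoCA and not on ADAS-Cog. The calculation covers CDR only; MoCA, which may range from 7 to 25, was not modelled.

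**The result might steer who is treated.** No treatment-selection rule in the article is tied to this hypothesis, so that inference is not supported.

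**The interaction is weakly powered.** True, and it limits what can be claimed. It does not make a more precise estimate of a different quantity a test of H4.

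**Conclusion.** The concern holds in this form: the stated test does not address the stated hypothesis, because it cannot separate a difference in prognosis from a difference in treatment effect. That conclusion follows from the wording and needs no assumption.

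The size does rest on assumptions: a natural CDR difference of 0 to 2 points, a CDR 2 share of 30-50%, SD 4.9 and 126 active patients. The active-only test then has a false-positive rate for effect modification between about 5% and 62%, against about 5% for the interaction. The bias can run in either direction. The point concerns a named hypothesis but not the primary comparison, so it should be corrected without calling the main efficacy result into question.

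**What to change.** - Test H4 by an arm-by-CDR interaction on ADAS-Cog change in all randomised participants, with arm-by-MoCA as a supporting continuous version.
- Report active-minus-sham differences within CDR 1 and within CDR 2, with confidence intervals.
- Label the analysis exploratory and state its power: about 44-50% for a 3-point modification and 15-17% for 1.5 points, with the two active arms combined against sham.
- Keep the active-only correlation and describe it as prognostic in treated patients, not as a test of H4.
- Use the same hypothesis number in the hypotheses and analysis sections.

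The change needs no new patients, visits or data, because stratification by CDR is designed to place sham patients at both levels, and no change to the primary model. The real cost is precision: with an even CDR split the standard error rises from 0.87 for the active-only contrast to 1.51 for the interaction, so a null result would say little.
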